#### Implementation strategies

All 10 implementation strategies tailored for the study are specified in detail in Supplementary file 1 following reporting standards. Core implementation strategies are (1) local adaptation and tailoring of the intervention, (2) micro-learning videos, (3) three theme-based training days available at three different blocks throughout the semester. Completing two training days is mandatory before school nurses can recruit adolescents for the study. School nurses can attend training days throughout the study period as needed. (4) Digital group supervision with external intervention specialists will be held twice the first month after completing two training days, and then once a month throughout the study. School nurses can request (5) individual supervision if needed, and they can call supervisors during regular office hours. Supervisors call school nurses in cases of fidelity drift, consistently low scores on functions, or a halt in recruitment and schedule supervision if needed. A final core implementation strategy is (6) relationship-building and ways of being, which is a strategy developed for the implementation team to build trusting, respectful, and professional relations with school nurses and leaders by adhering to core values (being structured, empathetic, and facilitative). Additional implementation strategies for the study include (7) audit and feedback lite, (8) continuous adaptation, (9) leader nudging and engagement, and (10) multi-level system dissemination. A manuscript is in preparation, reporting micro-theories of how each implementation strategy works to address important implementation determinants [54–56], and the system dynamics of the implementation of Kort over time [57].

#### Theory of change

 Figure 1 depicts a conceptual model illustrating the hypothesized mechanisms by which the intervention can lead to improved mental health and well-being in adolescents. The model includes the proposed main associations between each intervention element and proximal and distal outcomes. For each element, we have proposed a main mechanism of change (e.g., practicing Mindfulness is proposed to result in increased awareness and acceptance of emotions). In the model, motivation and alliance are proximal outcomes of the element Setting and reviewing goals. However, we believe these outcomes will affect adolescents’ engagement and adherence to the other elements and subsequently affect the associations between the other intervention elements and adolescent outcomes. The model has informed the development of the measurement system. Outcomes that are believed to develop slowly over time (e.g., mental health problems) are measured pre- and post, and outcomes believed to fluctuate daily or weekly (e.g., awareness) are measured using EMA and/or Daily diaries (see Table 3).

**Fig. 1 Fig1:**
[figure not shown]
Conceptual model of the intervention elements and outcomes. Note. The conceptual models depict the intervention element’s hypothesized primary linear mechanistic association with specific proximal outcomes. ER = Emotion Regulation

**Table 3 Tab3:** Outcomes, instrument, data collection method, informant, and timepoint for all measures

	Instrument	Method of Data Collection	Informant	Time- point					
				**T1**	**T2**	**T3**	**T4**	**EMA**	**DD**
**Intervention Outcomes**									
**Mental Health literacy**	Self-developed	Quant	A	x		x	x		
**Emotion Regulation (Trait)**	DERS-SF	Quant	A	x	x	x	x		
**Emotion Regulation (State)**	Self-developed	Quant	A					x	x
**Emotions (State)**	PANAS	Quant	A					x	x
**Mindfulness**	FFMQ-15^a^	Quant	A	x		x	x		
**Distorted Thinking/Cognitive Fusion**	CFQ	Quant	A	x		x	x		
**Internalizing and Externalizing Symptoms**	BFS	Quant	A	x	x	x	x		
**Well-being**	SWEMWBS	Quant	A	x	x	x	x		
**Functional Impairment**	Self-developed	Quant	A	x		x	x		
**Loneliness**	T-ILS	Quant	A	x		x	x		
**Self-compassion**	SCS-Y^b^	Quant	A	x		x	x		
**Sleep Quality**	Self-developed	Quant	A	x		x	x		
**Friendships**	Self-developed	Quant	A	x		x	x		
**Appropriateness**	IAM	Quant	SN	x		x	x		
**Feasibility**	FIM	Quant	SN	x		x	x		
**Usability**	IUS	Quant	SN	x		x	x		
**Determinants**									
**Alliance**	WAI-SR	Quant	A		x	x			x
**Demographics**	Self-developed	Quant	A, SN	x					
**Background variables (SES, ethnicity)**	Self-developed	Quant	A	x					
**Fidelity**^**c**^	Self-developed	Quant	SN						
**Adherence**^**d**^	Self-developed	Quant	A						x
**Readiness for change**	Readiness for Change Measure	Quant	SN	x		x	x		
**Implementation intentions**	MISII	Quant	SN	x		x	x		
**Experiences with responding to questionnaires **	Selv-developed	Quant	A						

*A* adolescent, *SN* school nurse, *EMA* ecological momentary assessment, *DD* daily diary

^a^Three subscales were selected (Describing, Non-judging, and Non-reactivity)

^b^Two subscales were selected (Kindness and Judging)

^c^A short fidelity survey is filled out by the SN after every consultation

^d^There is a total of 24 different adherence questions, and which ones adolescents receives depends on the elements and components school nurses reports to have used in a given consultation

### Data collection and outcomes

Table 3 depicts outcomes, instruments, data collection methods, informants, and time points for all measures used in the study. The time points correspond to two weeks prior to the start of the intervention (T1), once the adolescent completes the intervention (dynamic post measure, T2), 11 weeks after the intervention begins (T3), and again 11 weeks after T3 (T4) to serve as pre- post- and follow up assessments, respectively. The experience sampling measures will have a two-week baseline assessment between T1 and the intervention start.

#### Primary outcome measures

##### Implementability of the Kort intervention

School nurses will report on the perceived implementability (acceptability, feasibility, appropriateness, usability) of the Kort intervention using the Intervention Appropriateness Measure (IAM [48]), the Feasibility of Intervention Measure (FIM [48]), and the Intervention usability scale (IUS [49]) pre- and post-intervention and follow up (T1, T3, T4).

##### Adolescents’ proximal emotion regulation

(1) Daily experiences of affect and emotion regulation strategies will be measured using a daily diary, given every evening during the data collection period. (2) Momentary affect and emotion regulation strategies will be measured using momentary ecological assessment (EMA). Half of the sample will be randomized to daily diary only. The other half will be randomized to also report on momentary affect and emotion regulation strategies three times a day for four days every other week over two months (experience sampling period). Randomization is implemented digitally using sequential numbering in blocks of two participants (the first participant in the block is given a random value of 0 or 1, and the second is given the remaining value). There is no human assignment to conditions, the randomization result is automatically implemented by the data collection system. Supplementary file 2 depicts the data collection infrastructure and provides technical specifications of the experience sampling system.

##### Effectiveness of the intervention

Adolescents self-reported emotion regulation and mental health will be measured using Difficulties in Emotion Regulation Scale short form (DERS-SF), Behavior and Feelings Survey (BFS), and the short Mental Well-Being (SWEMWBS) scale at T1, T2, T3, T4.

#### Secondary outcomes and determinants

##### Intervention fidelity

(1) School nurses will complete a brief dynamic questionnaire about intervention fidelity after each consultation with adolescents, following a “flexibility for function” conceptualization of intervention fidelity. The fidelity questionnaire includes items about which core elements were used in the consultation, to what degree functions of each chosen core element were achieved, to what degree that elements’ core components were used, and to what degree the core components were adapted, which then prompts a free text option to provide details about the adaptation. The total fidelity battery consists of 38 items, however, the dynamic logic of it ensure nurses rarely answer more than 1–15 items per consultation (2) A post-consultation fidelity response from the school nurse prompts a corresponding dynamic fidelity questionnaire to the adolescent the same day about the core elements used in that consultation. The questionnaire also includes items about the alliance with the school nurse. This questionnaire will appear together with the adolescents’ daily diary questions that day and has a total of 24 items (12 of these are self-made). (3) School nurses will also take audio recordings of each consultation with the adolescents. Recordings will be analyzed using a newly developed fidelity coding framework corresponding to the fidelity questionnaire and with more focus on quality and competence in delivery, alliance, and communication (see qualitative analyses on page 20–21 for details).

##### Implementation determinants

Measures of implementation determinants include Innovation Specific Implementation intentions [50] and a Readiness for Change measure [51] measuring individual (e.g., openness to change, stress, job satisfaction, self-efficacy) and organizational (e.g., capacity, quality assurance routines, work climate) determinants of implementation. Both measures are administered to school nurses at T1, T3 and T4.

##### Adolescents’ health and quality of life

 Secondary measures of adolescents’ health and quality of life are administered at T1, T3 and T4, and include measures of mental health (Behavior and Feelings survey [58]), well-being (Short Warwick-Edinburg Mental Well-Being Scale [59]), mindfulness (three subscales of the Five-Factor Mindfulness Questionnaire; Describing, Non-Reactivity, & Non-Judging [60]), cognitive fusion (Cognitive Fusion Questionnaire [61]), self-compassion (two subscales of the Self-Compassion Scale for Youth, [62]; Self-kindness & Self-judging [63]), loneliness (the Three Item Loneliness Scale), friendship (subscale for Peers and Social Support from KIDSCREEN-27 [64], mental health literacy (seven self-developed items asking the adolescents whether they agree with statements about what is important for mental health), functional impairment (two self-developed items asking to what extent mental health symptoms impact adolescents’ daily lives), sleep and screen time use (seven self-developed items). Figure 2 depicts the experience sampling and measurement timepoints.

**Fig. 2 Fig2:**
[figure not shown]
Experience sampling in the experimental groups. Note. The dynamic T2 will be sent when school nurse prompts in the fidelity measure that they have completed the intervention. This can be done up until T4. T3 is sent when the experience sampling ends, T4 is sent 11 weeks after T3

##### Adolescents’ and school nurses’ experiences with Kort and its value

The adolescent’s experiences of Kort and its value will be studied in a qualitative interview after T3. Additionally, adolescents will be asked about their experiences with the daily diary data collection, with three questions added to their regular daily diary. The questions will be asked twice, once in the middle of the intervention period and once towards the end. The school school nurses’ experiences with Kort, its implementation, and its value, will be studied in follow-up focus group interviews at the end of the study.

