The use of experience sampling allows for measuring ER in real-life settings by minimizing recall bias and increasing the likelihood of accurate reports [41]. However, the literature is not clear about the effects of frequent data collection on adolescent motivation and engagement. A meta-analysis of ecological momentary studies showed that financial incentives were the only significant predictor of compliance, whereas the design, sample characteristics, or number of assessments had little effect [42]. One study collected data daily from adolescents for 100 days and reported a response rate of 86% [43]. In the current study we will investigate the potential burden of frequent data sampling by asking half of the sample to answer daily questions and the other half to answer additional questions three times a day in bursts. Quantitative and qualitative information about the adolescents’ experiences with the data collection will help optimize an experience sampling system, balancing data quality with response burden to be used in future studies.

In sum, there is a need for novel scalable interventions targeting transdiagnostic processes (i.e., ER) within the adolescent population, with a focus on effectiveness, efficiency, and implementability in Norwegian frontline mental health services. Therefore, we have - together with researchers, practitioners, adolescents, and other stakeholders - co-designed an evidence-informed intervention targeting ER for wide delivery in school health services.

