#### Qualitative analyses

The audio-recordings of consultations between school nurses and adolescents will be transcribed verbatim and coded for fidelity based on the “flexibility for function” conceptualization of fidelity. We will code quality in working towards core functions of intervention elements, and what components (i.e., activities and exercises) were used with adolescents in the consultation. We will also code which problems and concerns the adolescent brings to the consultations, how working goals are formulated, as well as communication structure and quality, and common relationship factors such as trust, alliance, and empathy. In addition, we also will code adolescents’ expressions of emotional concerns using a validated and widely used coding tool; Verona Definition of Emotional Sequences (VR-CoDES [65]).

The interviews with adolescents will be transcribed verbatim and coded for their experiences with the intervention and experience sampling. We will analyze the transcribed interviews using inductive, reflexive thematic analysis [66]. The analysis will use the six-phase process for data engagement, coding and theme development by Clarke & Braun [66]: (1) data familiarisation; (2) systematic data coding; (3) generating initial themes from coded and collated data; (4) developing and reviewing themes; (5) refining, defining and naming themes; (6) writing the report.

The focus group interviews in the implementation planning were transcribed verbatim and analyzed thematically with a combination of inductive and deductive coding based on the COM-B theory of behavior and motivation [53] the Consolidated Framework for Implementation Research 2.0 [52], and implementability theory [33].

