### Considerations of ethics and unintended consequences

Participation in the study requires adolescents to spend time answering frequent questions about their emotions and how they respond to them. This will be time-consuming, and some may experience this as unpleasant, even though feedback from piloting the system with adolescents has been positive. Due to the time-consuming nature of the experience sampling measures, a compensation system has been developed for the adolescents (see rewards for questionnaire completion on page 20). We also monitor response frequencies and will pause the experience sampling prompts when adolescents have not responded for seven days.

We have taken careful precautions to prevent unintended negative consequences or harmful effects of participation from emerging. For instance, the intervention is co-designed with school nurses and adolescents to be safe and appropriate for adolescents in school health settings. Also, school nurses have the necessary competence to consider whether an adolescent requires assessment from a mental health professional and have regular routines for referring them to the appropriate health services. With school nurses meeting participating adolescents regularly throughout the study period, they can ascertain whether the adolescent is faring worse. Overall, since the adolescents we aim to recruit do not have clinical-level mental disorders, we view the utility of the project as outweighing the inconvenience for participating adolescents.

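### The quantitative burden questions are asked only inside the daily diary, so adolescents who are silent or paused when they are asked do not answer, and burden will tend to be understated

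*Protocol article*

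**What the plan says.** The article's section on adolescents' and school nurses' experiences with Kort states that "adolescents will be asked about their experiences with the daily diary data collection, with three questions added to their regular daily diary". On timing it adds: "The questions will be asked twice, once in the middle of the intervention period and once towards the end". The section on ethics and unintended consequences states: "We also monitor response frequencies and will pause the experience sampling prompts when adolescents have not responded for seven days". No rule for resuming the prompts appears in the article.

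Table 3 lists "Experiences with responding to questionnaires" as a quantitative adolescent measure and marks no time point for it in any column.

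The purpose is given at the end of the background section on studying emotion regulation as a dynamic process: "Quantitative and qualitative information about the adolescents’ experiences with the data collection will help optimize an experience sampling system". The Abstract also names response burden among the domains of the research questions and ties the micro trial to it.

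There is a second, qualitative source. The adolescents' "experiences of Kort and its value will be studied in a qualitative interview after T3", and under Qualitative analyses: "The interviews with adolescents will be transcribed verbatim and coded for their experiences with the intervention and experience sampling".

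**The concern.** The burden items travel on the instrument whose burden they measure. An adolescent who stops answering because the sampling is too much either leaves that evening's diary unanswered or, once paused, is not sent it. Whether an answer exists thus depends on the quantity being measured, and those missing are likely to be those with the highest burden.

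The protocol intends these data to guide the balance between data quality and response burden in later studies. Answers drawn mainly from those who coped would make the system look more tolerable than it was. The randomised contrast adds a second risk. If the EMA schedule causes more adolescents to stop, the EMA arm's respondents are the more selected group, and a descriptive comparison of burden by arm would lean towards making the heavier schedule look acceptable.

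**Working it through.** The document gives no figure for this point, so there is nothing to reproduce. The check is to follow the delivery route, then show how the bias would scale under stated assumptions.

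**Who can answer**

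- Delivery: three items in the evening diary, asked at mid-intervention and towards the end (section on experiences with Kort).
- Pause: sampling prompts are paused after seven days without a response (ethics section).
- Other delivery of the same items: none stated. The Table 3 row is blank throughout, including the daily diary column where the text places the items, so it neither confirms nor excludes T3.

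| Adolescent's diary status | Midpoint items | Late items |
|---|---|---|
| Answering throughout | can answer | can answer |
| Stops between the two askings | can answer | missed |
| Stops before the midpoint and does not resume | missed | missed |
| Silent on an asking occasion but not yet paused | missed if that diary is left unanswered | likewise |

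Any adolescent who is interviewed after T3 can describe the sampling, whatever their diary status.

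**How many**

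The nearest figure is in the power calculation: up to 15% dropout, 46 recruited. Assuming that dropout equals diary silence, 0.15 × 46 = 6.9, or about 7 adolescents missing from one or both askings. The true share of paused adolescents is not given.

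**How the bias scales**

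Let p be the share not answering, and g the amount by which their mean burden exceeds that of the respondents.

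- True mean = (1 − p) × respondent mean + p × (respondent mean + g) = respondent mean + p × g.
- Understatement = p × g.

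Illustrations only. The value g = 1.5 SD and all arm-specific stopping shares are assumptions without a source in the document:

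| Stopped, diary only | Stopped, diary + EMA | Understatement, diary only | Understatement, diary + EMA | Arm difference hidden |
|---|---|---|---|---|
| 15% | 15% | 0.15 × 1.5 = 0.225 SD | 0.225 SD | 0 |
| 10% | 20% | 0.10 × 1.5 = 0.15 SD | 0.20 × 1.5 = 0.30 SD | 0.15 SD |
| 15% | 35% | 0.225 SD | 0.35 × 1.5 = 0.525 SD | 0.30 SD |

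With equal stopping and an equal gap, burden is still understated but the arm contrast is not distorted. If stopping is unrelated to burden (g = 0), there is no bias.

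**Set against precision**

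With 46 / 2 = 23 per arm and full response, the standard error of a difference in means is √(2/23) = 0.29 SD, and the 95% half-width is 1.96 × 0.295 = 0.58 SD. The illustrated arm biases lie inside that.

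**The case against.** A reader might infer that adolescents who found the sampling too heavy are never asked about it. The document does not support that. The interviews take place after T3, outside the diary, and are coded for experience sampling. Anyone who stops after the midpoint had one chance to answer. The rule is a pause, and the technical specification of the sampling system is in Supplementary file 2, which is not shown.

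A reader might also infer that the EMA arm's view of its extra prompts is not sought. The item wording is not shown, the Table 3 label is general, and the Design section counts EMA as part of the experience sampling that the interviews cover. This needs clarifying, not assuming.

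Nor does the document support reading the concern as a threat to the micro trial. Research question 5 is about response rates, in which adolescents who stop count fully. No test of mean burden between arms is stated, and 23 per arm could not support a precise one. The stopping shares and the 1.5 SD gap have no source. In-diary items also have a merit of their own: they limit recall, which is the article's reason for experience sampling.

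All of this stands, and it narrows the point without removing it. The article does not say how many adolescents are interviewed or whether paused ones are among them, and reflexive thematic analysis does not replace a quantitative measure. The three items are the quantitative half of the promised information on burden, and as described they depend on continued compliance.

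**Conclusion.** The point holds in limited form. As described, the three quantitative items are answered only by adolescents still completing the diary on the two asking occasions. The data are therefore selected towards those who tolerated the sampling and will tend to understate burden, possibly more in the EMA arm if EMA causes more stopping.

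The conclusion rests on two assumptions: that stopping is at least partly related to burden, and that the article has not left out another delivery of these items. The direction follows from the first assumption. The size does not follow from the document, and any figure is an illustration. This is a cheap improvement to a secondary measure, and it does not affect the validity of the response-rate outcome.

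**What to change.** Keep the three in-diary items and repeat the same items at T3. According to the note to Fig. 2, T3 is sent when experience sampling ends. It is a questionnaire separate from the diary and is paid 50 NOK (section on rewards). For the EMA arm, make sure the T3 items cover the EMA prompts if the present wording does not. State in Table 3 when the items are asked. Use the T3 answers as the main quantitative burden measure and the in-diary answers as supplementary. Report the response to these items by arm and by pause status, and say how many paused adolescents were interviewed.

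The costs are a slightly longer T3, answers that are more retrospective than those in the diary, and some adolescents who stopped and still do not reply. An extra message sent when the pause is triggered would reach some of them sooner, but it works against the purpose of the pause and is not needed for this fix.

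The article gives December 2024 as the planned end of the study. If collection is complete, what remains is to report item response by arm and pause status, read the answers alongside the interviews, and state the selection as a limitation.
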